#### Cognitive anxiety, somatic anxiety and self-confidence

Cognitive anxiety, somatic anxiety, and self-confidence are secondary measures. Cognitive anxiety and self-confidence will be assessed before each performance (Q2), whereas somatic anxiety will be assessed before and after each performance (Q2 to Q6) with the Competitive State Anxiety Inventory – 2 Revised (CSAI-2R; for English [66], for French [67]). Five items (e.g., “I am concerned about performing poorly”) assess cognitive anxiety, seven items (e.g., “My heart is racing”) assess somatic anxiety and five items (e.g., “I’m confident of coming through under pressure”) assess self-confidence. Intensity of each item is rated on a 4-point Likert scale (1 = “not at all” to 4 = “very much so”). We have changed the instructions to make the inventory applicable to music performance and the internal consistency of this questionnaire is good (Cronbach’s alpha > .80 [68]).

#### Arousal, valence, control

The affective dimensions arousal, valence, and control are secondary measures assessed with the Self-Assessment Manikin (SAMq; for English version [69], for French version [70]) before and after each performance (Q2 to Q6). The SAMq consists of five manikins for each affective dimension. Each dimension is scored on a 5-point scale. Arousal ranges from 1 (low arousal) to 5 (high arousal). Valence ranges from 1 (negative valence) to 5 (positive valence). Control ranges from 1 (not in control) to 5 (in control).

#### Flow

Flow refers to the subjective experience of being immersed and absorbed in an activity and is suggested to be a state of consciousness that is conducive to high levels of performance. In this study, it is a secondary measure assessed after each performance (Q3) with the Flow State Scale-2 (FSS-2) (for English [71], for French [72]). It consists of 36 items, with four items for each of nine dimensions (“challenge-skill balance”, “merging of action and awareness”, “clear goals”, “unambiguous feedback”, “concentration on the task at hand”, “sense of control”, “loss of self-consciousness”, “transformation of time” and “autotelic experience”). Respondents indicate the extent to which they agree with each statement on a 5-point Likert scale from 1 “strongly disagree” to 5 “strongly agree” by referring to the just completed performance. Higher scores reflect more intense flow. The internal consistency of this questionnaire is good (Cronbach’s alpha >.80 [71]).

#### Negative and positive post-music performance thoughts

Negative and positive post-music performance thoughts are secondary measures assessed after each performance (Q6) with the 23-item Post-Music Performance Thoughts Questionnaire [21] adapted from the Post-Event Rumination Questionnaire for public speech [73]. The questionnaire is divided into nine positive items (e.g., “My concert was good”) and 14 negative items (e.g., “I made a lot of mistakes”). Participants will be instructed to report to what extent they had each thought on mind since the end of the performance using a 5-point Likert scale ranging from 0 “not at all” to 4 “extremely”. The positive items score varies from 0 (no positive thoughts) to 36 (a lot of positive thoughts), and the negative items score varies from 0 (no negative thoughts) to 56 (a lot of negative thoughts). Internal consistencies of both scales are excellent [21].

#### Task engagement

The engagement in the task is a secondary measure assessed at the end of each performance session (Q6) with the question “To what extent did you try to give the best of yourself during the performance?”. Participants will answer using a 5-point Likert scale ranging from 1 “not at all” to 5 “very much so”.

#### Practice time

The amount of practice time for each session performance is a secondary measure assessed at the end of each performance session (Q6) with the question “How much time have you spent in the last 48 hours specifically preparing the musical piece you have just played?”. Participants will respond by indicating a numerical value.

#### Measures of the final online questionnaire

##### *Trait anxiety*

Trait anxiety will be assessed with the trait scale of the State-Trait Anxiety Inventory for adults (for English version [50], for French version [51]. This questionnaire consists of 20 items (example item: “I am a steady person”) that are rated on a 4-point Likert scale (1 “almost never” to 4 “almost always”). The total score ranges from 20 to 80, with higher scores indicating greater trait anxiety. The test has good psychometric properties [50, 74].

##### *Social anxiety*

Social anxiety will be assessed with the self-reported version of the Liebowitz Social Anxiety Scale (for English version [75, 76], for French version [77]). This scale quantifies fear and avoidance of social interaction situations (12 items, e.g., “Calling someone you do not know very well”) and performance situations (12 items, e.g., “Acting, performing or giving a talk in front of an audience”) during the last week. The possible responses for experienced fear are 0 (none), 1 (mild), 2 (moderate), or 3 (severe), and the possible responses for avoidance behavior are 0 (never), 1 (occasionally), 2 (often), or 3 (usually). The total score can range from 0 to 144 with higher scores indicating greater social anxiety. The test possesses good psychometric properties [78]*.*

##### *Depressive symptoms*

Depressive symptoms will be assessed with the Beck Depression Inventory-II (for English version [79], for French version [80]). This inventory is a unipolar questionnaire assessing depressive symptoms during the last 2 weeks with 21 items. Each item contains four sentences, which are coded from 0 (less close to depression, e.g., “I do not feel sad”) to 3 (*closest to depression*, e.g., “I am so sad or unhappy that I can’t stand it”). The total score can range from 0 to 63 with higher scores indicating more severe depressive symptoms. The test has good psychometric properties [79].

### Data-analytic strategy

Scores for self-report measures will be computed in accordance with guidelines. For cardiovascular and respiratory measures, scores will be computed for the 8-min sitting period, the 4-min performance period, and the three 5-min post-performance sitting periods, with focus on the 8-min sitting period, as this is the most relevant period with regard to our hypotheses. The area under the curve with respect to ground and to increase will be calculated for the salivary parameters [81].

Given the repeated measures design, we will use multilevel mixed-effects modeling following state of the art procedures [82, 83]. For the mediation analyses, we will follow the model suggested by Baron and Kenny [84]. The main predictors are performance session (private vs. public), general MPA level and their interaction. Where appropriate, skewed variables will be transformed. We will use an alpha level of 0.05 for all tests. We will perform sensitivity analyses adding control variables to the models if they are theoretically meaningful and significantly related to the outcome variable. Potential control variables are age, gender, use of hormonal contraceptives, menstrual cycle phase, BMI, smoking, trait anxiety, social anxiety, depressive symptoms, academic year, practice time, session order, and motion.

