
Many studies have shown that individuals exhibiting a cardiovascular challenge pattern prior to cognitive and motor tasks perform better than individuals exhibiting a cardiovascular threat pattern (e.g., [32–35]). Assessing challenge and threat with cardiovascular measures, as opposed to self-reports only, confers advantages because this approach does not rely on individuals’ ability or willingness to accurately report on their experiences, particularly given that nonconscious and irrational influences are affecting them [36, 37]. Furthermore, cardiovascular challenge-threat indices better predict performance than self-reported variables [28, 32, 38, 39], thus further highlighting the usefulness of these physiological parameters. Most studies on the link between challenge/threat states and task performance have used a between-group design. A within-person design can more conclusively show that cardiovascular activity predicts performance quality by excluding the alternative hypothesis that individuals who possess greater ability at a task are more likely to react with a challenge state [28, 40]. Anxious pianists reported lower expectations of being able to complete several tasks relating to piano performance than non-anxious pianists [3], suggesting that increasing levels of MPA might be associated with greater threat/lesser challenge.

The aim of this study is to investigate in university music students (1) whether the differences in their psychophysiological responses and in their MPQ between a private performance and a public performance vary significantly as a function of their general MPA level and (2) whether the cardiovascular CTI and the resources-demands differential are significant mediators of the relationship between the general MPA level and the MPQ. We aim to test the following hypotheses:

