### Sample size calculation

The sample size calculation refers to the first three sets of hypotheses, which we consider to be the critical ones. The power computations are based on a model by which the effect of general MPA level on MPQ follows two paths, direct and indirect. In the indirect path, MPA acts on the cardiovascular CTI, which acts on MPQ. The computations rely on the repeated simulations of such a model. First, we fix the distributional parameters of MPA. We obtained a mean (*M*) of 45 on the STAI-S scale and a standard deviation (*SD)* of 12 [8]. We assume that general MPA level influences deltaCTI, i.e., the difference in CTI between private and public performance sessions. To simulate realistic values for deltaCTI, we rely on [85] who reported a difference in the cardiovascular CTI between a “challenge” group and a “threat” group of 0.9. Thus, we assume *M* = 0.9 for deltaCTI. Moore et al. [85] used a two-group design, while we use a repeated-measures design. To estimate *SD* of deltaCTI, we rely on [8] who used a similar design as in the planned project. In their study, *M* and *SD* of deltaHR between private and public sessions were 28 and 16, respectively. Assuming similar coefficients of variation for deltaHR and deltaCTI, we obtain *SD* = 0.9*16/28 = 0.5 for deltaCTI. From knowledge about distributions of general MPA level and deltaCTI and assuming normal distributions and linear relationships, we can deduce the equation of the linear regression from the following variance components: Var(deltaCTI) = variance of deltaCTI, Var_Res_ = residual variance, Var(MPA) = variance of MPA. The slope beta_deltaCTI_MPA_ is the square root of (Var(deltaCTI) – Var_Res_)/Var(MPA), and the intercept is mean(deltaCTI) - beta_deltaCTI_MPA_*mean(MPA). Defining the effect size using Cohen’s [86] η^2^, where η^2^ = (Var(deltaCTI)-VarRes)/ Var(deltaCTI), the model relating MPA and deltaCTI is specified. Next, we specify the effect of deltaCTI on deltaMPQ, where deltaMPQ is the difference in MPQ between public and private performance sessions. We assume a linear relationship with slope beta_deltaMPQ_deltaCTI_. Without any loss of generality, we can specify the linear relation without intercept and with residual *SD* = 1. Thus, the indirect effect of MPA on deltaMPQ is beta_indir_ = beta_deltaCTI_MPA_*beta_deltaMPQ_deltaCTI._ Next, we assume that there is also a direct effect given by the slope beta_dir_, which is determined by the assumed mediated proportion (MP): beta_dir_ = beta_deltaCTI_MPA_*beta_deltaMPQ_deltaCTI_*(1-MP)/MP. In summary, given a simulation of MPA, we simulate deltaCTI and deltaMPQ = beta_deltaMPQ_deltaCTI_ *deltaCTI + beta_dir_*MPA + e, e ~ N(0,1). Finally, we define that small-to-medium effects (according to [86] criteria for interpreting η^2^) of MPA on deltaMPQ, MPA on deltaCTI and deltaCTI on deltaMPQ and MP between 20 and 30% are scientifically meaningful. By running 10′000 simulations of the aforementioned model with different combinations of the parameters, we determine that these effects are significant at α = 0.05 and power > 0.80 with a sample of 100 participants.

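### The Hypothesis 3 mediation analysis relies on the Baron-Kenny steps, names no estimate or interval for the indirect effect, and is not tied to the change-score model used for its power

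*Protocol article*

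**What the plan says.** The Data-analytic strategy gives the general model: "Given the repeated measures design, we will use multilevel mixed-effects modeling following state of the art procedures [82, 83". It adds "The main predictors are performance session (private vs. public), general MPA level and their interaction", and for Hypothesis 3, "For the mediation analyses, we will follow the model suggested by Baron and Kenny [84". It does not state how the mediator (the CTI or the resources-demands differential) enters the model, or whether it is centred. No test, estimate or interval for the indirect effect appears.

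In the Background, the hypotheses on challenge-threat, MPQ, state anxiety, respiration and saliva are all worded on public-minus-private change scores. Hypothesis 3 is not. The Background also gives a reason for comparing a person with himself or herself: "A within-person design can more conclusively show that cardiovascular activity predicts performance quality by excluding the alternative hypothesis" that abler performers are the ones who respond with challenge.

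The Sample size calculation counts Hypothesis 3 among the three critical sets. It simulates deltaCTI and deltaMPQ: "In the indirect path, MPA acts on the cardiovascular CTI, which acts on MPQ". An indirect slope and a mediated proportion (MP) of 20–30% parameterise the simulation. The conclusion is "power > 0.80 with a sample of 100 participants", for "small-to-medium effects (according to [86] criteria for interpreting η^2" on three paths: MPA on deltaMPQ, MPA on deltaCTI, and deltaCTI on deltaMPQ.

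**The concern.** There are two separate issues.

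- **The criterion.** The classical steps declare mediation only if the total effect, path a (MPA to mediator) and path b (mediator to MPQ given MPA) are each significant. Mediation is the product a×b. A significant total effect is not needed for a×b to differ from zero, so that step can only remove true positives. The steps also yield no size or precision for the indirect effect, although the power model is built around it.
- **The scale.** The stated model has session as a predictor, so it works on session values. If the CTI is entered as measured in a random-intercept model, path b becomes a weighted mixture of the within-person and the between-person association. That readmits the ability explanation that the Background wants excluded. On change scores this cannot happen.

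At stake is whether a critical hypothesis is missed when true or, under one reading of the model, supported when false.

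**Working it through.** **The plan's own figures.** SD of deltaCTI: 0.9 × 16/28 = 0.514, which agrees with the stated 0.5. Power above 0.80 cannot be reproduced, because the η² values, the sidedness and the mediation criterion are not given. For one regression slope at N = 100 (noncentral t, two-sided 0.05), power is 0.41 at η² = 0.03, 0.71 at 0.06 and 0.81 at 0.075. It reaches 0.80 at about 0.074. One-sided, it is 0.81 at 0.06.

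**Inputs.** From the article: N = 100, "We will use an alpha level of 0.05 for all tests", MP 20–30%, and direct slope = a×b×(1−MP)/MP. Assumed: two-sided tests and the η² values below.

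**Power, setting 1: η² = 0.06 for MPA on deltaCTI and for MPA on deltaMPQ.** In standardised units a = √0.06 = 0.245 and the total effect c = 0.245. Since a×b = MP × c, it follows that b = MP. At MP = 0.25, a×b = 0.061 and the direct effect is 0.245 × 0.75 = 0.184. Simulated power:

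| MP | Three steps | Interval on a×b | Ratio |
|---|---|---|---|
| 20% | 0.27 | 0.36 | 0.75 |
| 25% | 0.39 | 0.50 | 0.78 |
| 30% | 0.44 | 0.58 | 0.76 |

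Other runs of this setting, with MP 24.5% in the middle row and either a percentile bootstrap or joint significance of a and b as comparator, differed by up to 0.06 in the middle row and 0.03 in the others.

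**Power, setting 2: equal η² for path a and for path b (partial).**

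| η² | MP | Three steps | a and b jointly |
|---|---|---|---|
| 0.03 | 20 / 25 / 30% | 0.06 / 0.05 / 0.03 | 0.16 / 0.16 / 0.16 |
| 0.06 | 20 / 25 / 30% | 0.43 / 0.34 / 0.28 | 0.49 / 0.47 / 0.49 |
| 0.10 | 20 / 25 / 30% | 0.81 / 0.80 / 0.76 | 0.81 / 0.81 / 0.81 |

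As a check at η² = 0.06 and MP 25%: simulated power is 0.688 for a and 0.683 for b, and 0.688 × 0.683 = 0.470, against 0.469 simulated for both. Adding the total-effect step brings this to 0.338, a ratio of 0.338/0.469 = 0.72. A Monte Carlo interval on a×b gives 0.45 and the Sobel test 0.26. One-sided, the same setting gives 0.50 for three steps and 0.62 jointly.

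**False mediation.** Two sessions, N = 100, true within-person CTI–MPQ slope zero, a and total paths at r = 0.277, REML random-intercept model with uncentred CTI, all three steps required. The between-person correlations and the person-variance shares are assumptions.

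| Between-person r | Person-variance share 0.3 / 0.6 / 0.8 |
|---|---|
| 0.2 | 0.06 / 0.11 / 0.15 |
| 0.3 | 0.10 / 0.20 / 0.28 |
| 0.5 | 0.23 / 0.50 / 0.57 |

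At r = 0 the rate is 0.02. The same criterion on change scores gives 0.01–0.02 throughout.

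**The case against.** The strongest reply is that the article can be read coherently. The three paths in the Sample size calculation correspond to the total effect, path a and path b on change scores, so that section may show how the mediation model is meant. The cited state-of-the-art mixed-model procedures could include centring, and an article may leave that to a fuller plan. This largely stands: uncentred entry is an inference, and the false-mediation figures are conditional on it.

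Two stronger readings are tempting and are not supported.

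- A reader might infer that the plan never tests the indirect effect and that the steps themselves create false mediation. Joint significance of a and b is a valid test of a×b, and on change scores the steps gave false mediation in only 0.01–0.02 of runs. Their fault is lost power and the absence of an estimate.
- A reader might quote rejection rates for path b under the uncentred model, about 17–70% at assumed correlations of 0.2–0.4. Those are rejections of one step, not declarations of mediation, and they too rest on assumed correlations and person-variance shares.

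It can also be said that Hypothesis 3 concerns mediators of a relationship that Hypothesis 2 posits, so asking for that relationship first is coherent. It is, but Hypothesis 2 already tests it, and repeating it as a gate only lowers power.

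Finally, most of the distance to 0.80 comes from the effect size at N = 100, not from the method. An interval on a×b also falls short at η² = 0.06, and the three steps beat the Sobel test there (0.34 against 0.26).

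**Conclusion.** The concern holds in limited form. The article commits to the Baron-Kenny steps for a critical hypothesis, names no estimate or interval for the indirect effect, and leaves Hypothesis 3 unattached to the change-score model behind its power.

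With setting 1 at η² = 0.06, the total-effect requirement gives up about a quarter of the attainable power (0.27–0.44 against 0.36–0.58). The loss depends on the effect sizes: in setting 2 at η² = 0.10 it is between nothing and 0.05. The article gives no η² values, so no single figure is the protocol's own.

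The risk of false mediation, about 0.06–0.28 at assumed between-person correlations of 0.2–0.3, exists only if the mediator enters uncentred. The article does not say so, and the change-score wording elsewhere points the other way.

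This is worth correcting before the Hypothesis 3 analysis is run. It does not show that the planned analysis is invalid.

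**What to change.** - State that Hypothesis 3 is tested on change scores: deltaCTI on MPA for path a, and deltaMPQ on deltaCTI adjusted for MPA for path b. Alternatively, keep the mixed model and person-mean-centre the mediator.
- Report a×b with a percentile bootstrap 95% confidence interval, and make exclusion of zero the criterion for mediation.
- Drop the requirement of a significant total effect. Hypothesis 2 still tests that effect.
- Apply the same to the resources-demands differential, for both self-rated and expert-rated MPQ.
- Restate the Hypothesis 3 power for this criterion, giving the η² values and the sidedness.

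The cost is some wording and a small amount of extra analysis, with no new data. The downside is a less favourable stated power: at η² = 0.06 in setting 1, about 0.36–0.58 at N = 100.

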**Methods:**

We will test 100 university music students reporting general MPA levels ranging from low to high. They will perform privately (i.e., without audience) and publicly (i.e., with an audience) on two separate days in counterbalanced order. During each performance session, we will record their cardiovascular and respiratory activity and collect saliva samples and self-reported measures. Measures of primary interest are self-reported anxiety, the resources-demands differential, the cardiovascular challenge-threat index, sigh rate, total respiratory variability, partial pressure of end-tidal carbon dioxide and the salivary biomarkers cortisol, dehydroepiandrosterone, and alpha-amylase. Both, the participants and anonymous experts will evaluate the performance quality from audio recordings.

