*Relationship between general MPA level and challenge-threat*. Higher general MPA level is associated with greater increase in threat from the private to the public performance: With increasing general MPA level, change scores (public minus private) of the cardiovascular CTI and the resources-demands differential (self-rated resources minus self-rated demands) decrease.*Relationship between general MPA level and MPQ.* Higher general MPA level is associated with greater decrease in self-rated and expert-rated MPQ from the private to the public performance: With increasing general MPA level, change scores (public minus private) of self-rated and expert-rated MPQ decrease.*The mediating role of challenge-threat.* The cardiovascular CTI and the resources-demands differential are significant mediators of the relationships between general MPA level and self-rated and expert-rated MPQ.*Relationship between general MPA level and state anxiety.* Higher general MPA level is associated with greater increase in state anxiety from the private to the public performance: With increasing general MPA level, change scores (public minus private) of state anxiety increase.*Relationship between general MPA level and respiration.* Higher general MPA level is associated with greater increase in sigh rate and total respiratory variability and greater decrease in P_et_CO_2_: With increasing general MPA level, change scores (public minus private) of sigh rate and total respiratory variability increase, whereas change scores of P_et_CO_2_ decrease.*Relationship between general MPA level and salivary measures of HPA axis activity and SAM axis activity.* Higher general MPA level is associated with greater increase in sC and greater decrease in sDHEA, anabolic balance and sAA: With increasing general MPA level, change scores (public minus private) of sC increase, whereas change scores of sDHEA, anabolic balance and sAA decrease.

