### Habituation session

Participants will be tested individually. Upon arrival to the lab, the experimenter will explain the study protocol to the participant and obtain written consent. This will be followed by the measurement of participant’s body height and weight, which are used to compute the body mass index (BMI). Afterwards, the participant will be familiarized with the physiological measurements. The experimenter will show the different instruments and explain their function. Afterwards, the sensors of the four devices Finometer, VU-AMS, BioRadio and Capnostream will be applied, and the participant will be asked to sit for 8 min alone. After removing the sensors of the Finometer and the Capnostream, the participant will be invited to play his/her instrument for a few minutes. Information about the comfort level regarding the sensors during the two periods will be obtained, and adjustments to the sensors will be made if required. The participant will also be familiarized with the saliva sampling procedure.

In the second part of the habituation session, the participant will be presented with a list of instrument specific music pieces from which he/she will have to choose one to perform during the following performance sessions. The pieces belong to the standard repertoire usually required for auditions, competitions and exams. The duration of the pieces is between 3 min and 4 min and 30 s (e.g., first 4 min of the solo parts of the clarinet concerto in A major, K. 622 by W.A. Mozart). We will provide the participants with the exact number of bars to perform and require them to perform the selected pieces by heart and without accompaniment during the two performance sessions. Participants will be given up to 2 days to choose their music piece. Finally, the experimenter will give the participant the following information about the upcoming performance sessions: the session order (private before public session or vice versa) and the audience composition (composed of the experimenter and five to seven music connoisseurs including two experts who will rate their MPQ). The experimenter will also explain the MPQ Scale to them.

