### Private and public performance sessions

One month after the habituation session, the participant will come to our laboratory for the two performance sessions. For each participant, the two sessions will take place 2 days apart (e.g., Monday and Wednesday) at the same time of the day. Participants will be scheduled at either 1 pm or 3.45 pm. The procedures of the two sessions are identical, except for the fact that the participants will perform without audience in the private session and in front of an audience of six to eight persons in the public session. Participants are randomly assigned to one of the two possible orders. The procedure of a performance session is shown in Fig. 2.

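### Randomised session order is left out of the main models and admitted only behind a significance screen; session position should be a fixed term in every primary and mediation model

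*Protocol article*

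**What the plan says.** The abstract states that students perform privately and "publicly (i.e., with an audience) on two separate days in counterbalanced order". The section on the performance sessions adds: "Participants are randomly assigned to one of the two possible orders". The Habituation session section treats order as an attribute of the participant: "the session order (private before public session or vice versa").

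The Data-analytic strategy section gives the model class: "Given the repeated measures design, we will use multilevel mixed-effects modeling following state of the art procedures". It then gives the terms: "The main predictors are performance session (private vs. public), general MPA level and their interaction". Neither order nor first-versus-second position is among them. Other variables enter under this rule: "We will perform sensitivity analyses adding control variables to the models if they are theoretically meaningful and significantly related to the outcome variable". The candidate list runs from age, gender and BMI to "academic year, practice time, session order, and motion". The form in which order would enter is not stated.

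The hypotheses in the Background are worded as slopes of change scores on MPA, for example "With increasing general MPA level, change scores (public minus private) of the cardiovascular CTI and the resources-demands differential" falling. The simulation model in the Sample size calculation section is also in change scores and contains no order or position term.

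**The concern.** This is a two-session crossover in which the order of the conditions is randomised. Whatever differs between a first and a second session enters the public-minus-private change score with a plus sign for students who play privately first and a minus sign for the others. If the model has no term for it, that variation goes into the residual. Playing the same memorised piece again 2 days later makes such a difference plausible.

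The stated rule may not catch it. A screen on outcome level compares the two order groups on their average over both sessions, and a pure first-versus-second effect leaves those averages equal. Even if order passed the screen, it would reach only a sensitivity analysis, and as a between-person main effect in the mixed model it would not change the test of interest.

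The stakes are precision for the session-by-MPA test (hypotheses 1, 2 and 4 to 6) and, for hypothesis 3, possible confounding of the path from the mediator to performance quality.

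**Working it through.** **Inputs from the documents.** N = 100, alpha 0.05, power above 0.80, MPA mean 45 and SD 12, deltaCTI mean 0.9 and SD 0.5 (Data-analytic strategy and Sample size calculation).

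**Assumptions.** Two-sided test; equal allocation to the two orders; period effect π (second minus first session) in residual SDs of the change score. The documents give no value for π, so a range is shown.

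**1. The plan's own figures.** The SD reproduces: 0.9 × 16/28 = 0.514, rounded to 0.5. Power above 0.80 cannot be reproduced, because the effect sizes are described only as small to medium. For the slope of deltaCTI on MPA, n = 100 reaches 0.80 two-sided at η² of about 0.074.

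**2. What an order main effect does.** With two sessions per person, the session-by-MPA test rests on the within-person difference. A between-person term is the same in both sessions and cancels. In one simulated data set (period effect 0.5 SD of deltaCTI), the session-by-MPA coefficients were:

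| Model | Estimate | SE |
|---|---|---|
| session × MPA | 0.188 | 0.0570 |
| + order main effect | 0.188 | 0.0570 |
| + first/second position | 0.171 | 0.0527 |
| + session × order | 0.171 | 0.0527 |
| change score on MPA | 0.188 | 0.0570 |
| change score on MPA + order | 0.171 | 0.0527 |

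The last three adjusted rows are the same analysis. The shift in the estimate belongs to this one data set and is not evidence of bias.

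**3. What a screen on level sees.** With π added to the second session, each person's two-session average rises by π/2 in either order. The order groups do not differ on average, so order tends to fail the screen.

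**4. Precision of the session-by-MPA test.** The change score shifts by +π or −π, which adds π² to a residual variance of 1. Taking η² = 0.073, f² = 0.073/0.927 = 0.0787, and the noncentrality without the term is √(100 × 0.0787/(1 + π²)):

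- π = 0: √7.87 = 2.81, power 0.79
- π = 0.25: √(7.87/1.0625) = 2.72, power 0.77
- π = 0.5: √(7.87/1.25) = 2.51, power 0.70
- π = 0.75: √(7.87/1.5625) = 2.24, power 0.60

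With the term, power stays at 0.79 for every π. Simulation with MPA drawn at random gives slightly lower values: about 0.76 against 0.78 at 0.25, about 0.68 against 0.77 at 0.5, and about 0.59 against 0.78 at 0.75. On the CTI scale the residual SD is 0.5 × √0.927 = 0.48, so 0.25 and 0.5 residual SD correspond to 0.12 and 0.24 CTI units.

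**5. Mediation path.** Suppose deltaCTI has no effect on deltaMPQ, but both carry the same ±π by order. Given MPA, the regression of deltaMPQ on deltaCTI then has expected slope π²/(1 + π²) in residual-SD units: 0.0625/1.0625 = 0.06 at π = 0.25, and 0.25/1.25 = 0.20 at π = 0.5. The simulated false-positive rate for this path at n = 100 is:

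| π on both | Order omitted | Order included |
|---|---|---|
| 0 | 0.05 | 0.05 |
| 0.25 | 0.09 | about 0.05 |
| 0.5 | 0.53 | about 0.05 |
| 0.75 | 0.98 | about 0.05 |

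Period effects of opposite sign would push the path in the other direction.

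**The case against.** The case for leaving the plan as it is has several sound parts.

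- **The coding is open.** The article nowhere says that order enters as a between-person main effect. The hypotheses are in change scores, and in a change-score model order as a plain covariate removes the period effect. If the screen were run on change scores, it could also detect one. This stands, so the statement about the main effect holds only for the mixed-model reading.
- **The design already reduces period effects.** About a month earlier, participants visit the laboratory, wear all four devices, play their instrument and rehearse saliva sampling. The two sessions share time of day and procedure. Laboratory novelty and unfamiliar sensors are therefore weak explanations. Repetition of the same piece remains.
- **An article condenses.** A list of main predictors need not be every model term. But the article does say where order goes: to sensitivity analyses, behind a screen. That is a stated rule, not an omitted detail.

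A reader might go further and infer that the study is underpowered or that its main result is biased. The documents support neither. They give no period effect. The planning SD is scaled from private-to-public heart-rate differences in a similar design and may already contain period variance. In that case unadjusted power stays at 0.80, and adjustment raises it to 0.83 or 0.91 for period effects of 0.25 or 0.5 SD of deltaCTI. Order is randomised independently of MPA, so omitting it does not bias the MPA slope in expectation. Chance imbalance of MPA between the orders is part of the sampling error already counted.

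**Conclusion.** The point holds as a free improvement to a stated rule. A randomised design factor should be in the models by design, and here it is optional, screened and confined to sensitivity analyses under any coding.

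The gain depends on a period effect of unknown size. For the session-by-MPA test, the loss from omission is about 2 points of power at 0.25 residual SD and about 9 at 0.5, for an assumed η² of 0.073. For the mediation analysis the matter is more than efficiency: a period effect shared by CTI and performance quality makes order a common cause of mediator and outcome, and the false-positive rates above follow from that assumption. The claim of power above 0.80 at 100 participants is neither confirmed nor refuted here.

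**What to change.** In the Data-analytic strategy section, state that session position (first or second) is a fixed effect in every primary and mediation model, whatever its p-value. Session by order in the mixed model is equivalent, as is randomised order as a covariate in change-score models. State the coding.

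The order main effect may stay in the list of sensitivity variables: in a two-session crossover it gives a look at carryover or a session-by-position interaction, and the position term does not replace it.

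The cost is one sentence and one degree of freedom. At n = 100 with no period effect, the simulated power is 0.78 with or without the term. Design, data collection and sample size do not change.
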